#### Pilocarpine study

Patients will be recruited in two hospitals (one university hospital, one regional hospital) and nursing homes affiliated with The Living Lab in Ageing & Long-Term Care. Recruitment and identification of eligible patients will be carried out by the hospital’s palliative care consultants and nursing homes’ nurses based on the inclusion and exclusion criteria. When an eligible patient has been identified, the care teams will hand over an information letter and the research team will be notified. After a minimum of 1 day, the research team will perform an informative visit to explain the study procedures and the application of the drops, answer any questions and further assess eligibility. After 7 days of deliberation time, formal written informed consent will be obtained. The inclusion procedure will then be followed by (block) randomization of the patient to either pilocarpine or placebo using ALEA®. The randomization outcome will be blinded for both the patient and the researchers. After randomization, the study will officially commence as visualized by Fig. 1.

### Effect evaluation

An overview of the data collection process, including timing of data collection and instruments, is provided in Table 2. All outcome measures and research instruments have been synchronized between the two intervention studies, except for two: the adherence and side-effects questionnaires are only applicable to the pilocarpine study.

#### Baseline measures

Demographic characteristics of patients that will be collected are gender, age, care setting, primary diagnosis and co-morbidities, medication and treatment, presence of (partial) dental prosthesis and use of alcohol and nicotine. In addition, in the MEP study, the demographic characteristics of professionals that will be collected are function, years of experience, palliative care experience and education, and oral care experience and education.

#### Primary outcomes

The primary outcome is the effectiveness of the intervention in reducing dry mouth complaints in patients with a life-limiting condition or frailty. This is measured by the percentage responders at week 4, for which a clinically relevant response is defined as at least a 2-point reduction on the 11-point numeric rating scale (NRS). The NRS is a frequently used instrument in both clinical practice and research settings to score symptom severity, such as for pain, nausea and sleep [31]. The NRS for dry mouth ranges from 0 = no dry mouth symptoms to 10 = worst possible dry mouth symptoms [1, 7].

#### Secondary outcomes

Secondary outcomes include effect durability, (mouth-related) quality of life, patient-reported functional status, global perceived effect by participants, cost-effectiveness, adherence and side-effects. The specific research instruments per outcome used are detailed in Table 2.

Effect durability is measured by the percentage responders at week 8 and 12, as well as by changes in mean NRS dry mouth scores in the intervention versus the control group at all time-points. Effectiveness as perceived by the patient is measured by a 7-point scale (the Global Perceived Effect, GPE) [37] rating how much the patients’ condition has improved or deteriorated since the start of the study in both the control and intervention group. The global perceived effect is measured using a 7-point scale, rating how much the patients’ condition has improved or deteriorated since the start of the study for both the control and intervention group.

Changes in mouth-related quality of life is examined at all time-points between groups using two different validated questionnaires: the Geriatric Oral Health Assessment Index (GOHAI-NL) [33] and the shortened Summated Xerostomia Inventory (sXI-D) [32]. The GOHAI-NL consists of 12 oral health related items and three categories: physical function, psychosocial function and pain/discomfort. The sXI-D consists of 5 items, addressing dry mouth in general and consequences of dry mouth, such as difficulty eating and swallowing. In addition, functional status and overall quality of life are measured by a validated patient-reported functional status scale (from 0 = normal with no limitations to 4 = bed ridden, rarely out of bed) [37] and the EuroQol 5 Dimensions 5 Levels (EQ-5D-5L) questionnaire [34] respectively. The latter will also be used for the cost-effectiveness analysis and assesses quality of life in five dimensions: mobility, self-care, usual activities, pain/discomfort and anxiety/depression. The EQ-5D-5L is complemented by the iMTA (Institute for Medical Technology Assessment) Medical Consumption Questionnaire (iMCQ) for the cost-effectiveness analysis [38]. The iMCQ measures medical consumption, including medical and paramedical treatments or services, in- and outpatient care and medication.

Lastly, in the pilocarpine study the adherence and side-effects from either the pilocarpine or the placebo are measured by using short-form questionnaires.

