**Fig. 1 Fig1:**
[figure not shown]
Study procedures for the non-pharmacological (**a**) and pharmacological study (**b**) within the Dry mOuth Project. **a** The Mouth Education Program (MEP) study is a cluster non-randomized trial with a study period of 12 weeks and five visits per patient. **b** The pilocarpine study is a double-blind placebo randomized controlled trial with an active treatment period of four weeks and an optional expanded access period of eight weeks per patient. **c** A nested qualitative sub-study will be conducted during and after both studies. Abbreviations: CAU = care as usual, MEP = Mouth Education Program, UC = usual care; HCP = health care professionals; T0-12 = patient timeline at *t* = 0, *t* = 2, *t* = 4, *t* = 8 and *t* = 12 weeks

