#### Pilocarpine study

The pilocarpine study will investigate the effect of locally administered oral pilocarpine drops (3 × 5 mg per day) compared to placebo in reducing complaints of dry mouth in patients with a life-limiting condition or frailty.

Pilocarpine activates the muscarinic receptors, stimulating saliva secretion which in turn alleviates dry mouth symptoms. Systemic pilocarpine tablets have various parasympathomimetic adverse effects such as transpiration, flushing, headaches, dizziness and more [20]. The locally administered oral pilocarpine drops created for this study, however, are topical (non-systemic) and have previously been shown to have minimal adverse effects [21]. In our pilot study an optimal dosage regime was established of 5 mg pilocarpine in drops three times per day [21]. The placebo for this trial has the same qualitative composition, except for pilocarpine HCl, and has comparable traits in terms of texture, taste and look.

For four weeks each group will be instructed to administer 6 drops 3 times a day of either pilocarpine HCL (25 mg/ml) or placebo. Drops are administered left and right outside the molars and in front of the front teeth of the lower jaw, with 2 drops at each site of application. After the blinded 4-week active study period, every participant is offered an 8-week unblinded extension treatment period with off-label pilocarpine eye drops in order to establish longer term efficacy of pilocarpine and to offer active treatment to the placebo group (see also Fig. 1b).

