### Data analysis

#### Analysis of effect evaluation

All analyses will be carried out using statistical software that supports multi-level mixed model analyses, including the latest version of IMB SPSS Statistics. Demographic and baseline disease characteristic data will be summarized for each treatment group by presenting descriptive statistics. For continuous variables, we will use the mean and standard deviation (SD) in case of a normal distribution, or median and first and third quartile in case of skewed distribution. In case of missing data, we will use stochastic regression imputation to produce a synthetic part of the data to allow for an intention to treat analysis that includes all patients. For all analyses on primary and secondary outcomes a *p* value < 0.05 will be considered to indicate statistical significance. However, interpretation of these significant results will primarily focus on clinical relevance.

The primary outcome (percentage responders at 4 weeks) will be computed by using multi-level logistic regression analysis in the MEP study due to its cluster design, and linear regression analysis in the pilocarpine study taking the randomization stratification variable (sex) into account. Results will be expressed as odds ratio (OR) with a 95% confidence interval (CI).

All secondary outcome measures will be described in full using either mean and standard deviation median and interquartile range for continuous measures or count and proportion for categorical measures. Between-group differences in secondary outcomes at 4, 8, and 12 weeks (i.e., mean GOHAI-NL scores [33], mean PRFS scores [35], and patients’ Global Perceived Effect [37] dichotomized into success and no success) will be tested using multivariable generalized linear regression analysis with a link-function depending on the distribution of the variable (i.e. gaussian, or linear regression for continuous variables, binomial, or logistic regression for binary outcomes).

Cost-effectiveness analysis will be performed to examine both the costs and health outcomes of the interventions versus the control group, using the EQ-5D-5L [34], iMCQ [38] and factual costs of the medicine.

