#### Pilocarpine study

The pilocarpine study was submitted through the new Clinical Trials Information System (CTIS) and approved by the Medical Ethics Committee of Maastricht University Medical Center + . The risk classification analysis showed that the pilocarpine study entails moderate risk since pilocarpine is a registered drug for oral and ocular use. Case-reports and case-series indicate that topical pilocarpine administration has none or minor side effects (irritation of mouth and tongue). The burden of xerostomia on patient well-being outweighs the risk of side effects. Small studies and case reports suggest that local application has none or only minor side effects [20]. In the experimental group, benefits of participation may include relief of dry mouth symptoms and improved (oral-health-related) quality of life. Similar to the experimental group, the control group, will be offered unblinded expanded access to pilocarpine eye drops after 4 weeks and may therefore benefit from similar results.

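### In the pilocarpine study, between-arm results at weeks 8 and 12 compare immediate with delayed open-label access, so they cannot measure durability against placebo

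*Protocol article*

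**What the plan says.** **Design.** The Fig. 1 caption describes the pilocarpine study as a "double-blind placebo randomized controlled trial with an active treatment period of four weeks and an optional expanded access period of eight weeks per patient". Under Intervention and control, Pilocarpine study, the article says that "every participant is offered an 8-week unblinded extension treatment period with off-label pilocarpine eye drops in order to establish longer term efficacy of pilocarpine", and gives as a second purpose "to offer active treatment to the placebo group". Ethical considerations confirms that the control group "will be offered unblinded expanded access to pilocarpine eye drops after 4 weeks".

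**Outcomes.** Secondary outcomes states: "Effect durability is measured by the percentage responders at week 8 and 12, as well as by changes in mean NRS dry mouth scores". The rest of that sentence compares the intervention with the control group at all visits. The opening paragraph of Effect evaluation says that outcome measures are the same in both studies apart from adherence and side-effects.

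**Analysis.** Analysis of effect evaluation plans to test "Between-group differences in secondary outcomes at 4, 8, and 12 weeks" and names mean GOHAI-NL, mean PRFS and dichotomised GPE. On costs it says: "Cost-effectiveness analysis will be performed to examine both the costs and health outcomes of the interventions versus the control group". No time horizon is given. Table 2 schedules EQ-5D-5L and iMCQ at weeks 0, 4, 8 and 12.

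**The concern.** One outcome template serves two designs. It suits the MEP study, where the plan leaves controls on usual care through week 12. In the pilocarpine study the plan keeps nobody on placebo after week 4, yet the same intervention-versus-control wording runs on to week 12.

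The risk is a wrong conclusion on a named secondary outcome. If pilocarpine works and goes on working, placebo patients who take up the open drug improve too and the arms converge. Under the durability definition, that convergence would read as loss of effect. The extension was set up partly to show longer-term efficacy, and the planned contrast cannot show it.

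**Working it through.** **1. Who receives what, by original arm**

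| Period | Pilocarpine arm | Placebo arm |
|---|---|---|
| Weeks 0–4 | blinded pilocarpine | blinded placebo |
| Weeks 4–12 | open pilocarpine, if accepted | open pilocarpine, if accepted |

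The contrast is pilocarpine versus placebo only in the first row. In the second it is early versus delayed access, unblinded and with self-chosen uptake. Nothing in the article redefines weeks 8 and 12 as early versus delayed start, as within-arm, or as descriptive.

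**2. Reproducing the plan's own sample size**

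Inputs: difference 2 NRS points (Sample size, opening paragraph); SD 3.8 and 57 per group (Sample size, Pilocarpine study). Two-sided alpha 0.05 and power 0.80 are assumed here. The article gives 0.05 and 0.8 for the MEP study only, without saying one- or two-sided.

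n per arm = 2 × (1.960 + 0.842)² × 3.8² / 2² = 2 × 7.85 × 14.44 / 4 ≈ 56.7, rounded up to 57, or 114 in total. This matches, so the sample size is not in dispute.

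**3. Expected difference after week 4**

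Let c be the share of the pilocarpine arm on open drug and u the share of the placebo arm on open drug. Assume that the 2-point benefit is fully durable but present only while on drug. Then:

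- expected difference = 2 × (c − u)
- standard error = 3.8 × √(2/57) ≈ 0.712
- power ≈ Φ(difference / 0.712 − 1.960)

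| c | u | Difference (points) | Power |
|---|---|---|---|
| 100% | 0% | 2.0 | 80% |
| 100% | 25% | 1.5 | 56% |
| 100% | 50% | 1.0 | 29% |
| 100% | 75% | 0.5 | 10% |
| 100% | 100% | 0 | about 5% (alpha) |
| 80% | 80% | 0 | about 5% (alpha) |
| 50% | 80% | −0.6 | sign reversed |

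The drug effect is equally durable in every row. Only uptake changes, so the between-arm difference tracks uptake and not durability.

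Both shares are assumptions, because the article gives no uptake figure. The table covers the NRS only. GOHAI-NL, PRFS and GPE meet the same problem at weeks 8 and 12, but the article gives no effect size or SD for them.

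**The case against.** **The extension is openly described.** A careful reader will see that placebo control ends at week 4, and the comparison by original arm remains a valid randomised comparison of immediate with delayed start. This stands, and it is why that comparison need not be discarded. It does not turn the comparison into a measure of durability, which is the label the plan gives it.

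**The named tests are narrower than the outcome definition.** The between-group tests at 8 and 12 weeks list GOHAI-NL, PRFS and GPE, not NRS responders. In the durability sentence, the intervention-versus-control phrase follows the mean-NRS clause and may not govern the responder percentages. This stands: a between-arm test of responders at weeks 8 and 12 is a possible reading, not an explicit plan. Mean NRS change by arm and the three named tests are explicit.

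**Cost-effectiveness.** A reader might infer that costs and EQ-5D-5L are compared over 12 weeks and so diluted by open drug in the control arm. The visit schedule makes that possible, but no horizon is stated and week-4 data are collected. The text does not fix a 12-week contrast.

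**Within-arm reporting has its own bias.** Those who enter the extension and remain in it are selected, in a population where deterioration and death are expected. This also stands, so such results need to be labelled as uncontrolled.

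**Conclusion.** The mismatch is real. As written, the plan carries intervention-versus-control wording to weeks 8 and 12 in a study whose placebo control ends at week 4, and a lasting effect could be reported as not lasting. Under the assumptions of the illustration, power falls from 80% with no placebo-arm uptake to about 29% at 50% and about 10% at 75%. The true figure is unknown because uptake is not stated.

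A reader might go further and say that the expected difference is zero and that the test rejects in 5% of trials whatever the true durability. The documents do not support that. Zero requires full or equal uptake of an optional extension and no dependence on time on drug. At week 8, continuing early starters would have had 8 weeks of drug and delayed starters 4. If the effect waned with exposure, the arms could differ.

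The week-4 primary outcome, the sample size and the MEP study are unaffected. As only secondary outcomes are involved, this is a should-fix.

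**What to change.** For the pilocarpine study only:

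1. Limit pilocarpine-versus-placebo tests to weeks 2 and 4.
2. Describe weeks 8 and 12 within each original arm as uncontrolled extension data, with the numbers entering the extension and a statement of the selection this brings.
3. Label any between-arm result at those weeks as early versus delayed start, not as durability versus placebo.
4. State the cost-effectiveness horizon, and base any pilocarpine-versus-placebo contrast on the 4-week blinded period, using the week-4 EQ-5D-5L and iMCQ.

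Keep the 12-week comparison for the MEP study.

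The cost is wording in the protocol or SAP, with no change to visits, treatment or sample size. The sponsor gives up a long-term between-arm claim that the design cannot support.

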### Feasibility and acceptability evaluation

The DROP contains a nested qualitative sub-study to evaluate the feasibility and acceptability of either intervention. The main goal is to gain a multi-perspective insight into experiences with current guidelines and care for dry mouth symptoms, into barriers and facilitators within current care and within either intervention, and into feasibility of either intervention. To this end, in both studies, patients will be interviewed about their experiences with the intervention (MEP respectively pilocarpine) or control (CAU respectively placebo) through semi-structured interviews. In addition, in the MEP study, questionnaires on usual care (self-developed) and on implementation of health innovations (validated; [39]) will be administered to participating healthcare professionals. This will then be used to inform topic guides for focus groups which are held separately in each care setting, in both hospitals and nursing homes, and in each arm, in both control and intervention groups.

### Sample size

Sample sizes have been calculated based upon our expectation that both interventions, MEP and pilocarpine, lead to a clinically relevant lower dry mouth score, a minimum 2-point decrease on the 11-point numeric rating scale for dry mouth severity, as compared to CAU respectively placebo.

#### MEP study

For this study, we expect the intervention group (patients who follow the MEP) to have at least 25% more responders (patients with clinically relevant less dry mouth at 4 weeks) than in the control group (patients who receive CAU). To test the null hypothesis (expected difference in responders at 4 weeks of 25%) with a power of 0.8, an alpha of 0.05 and an intra cluster coefficient of 0.10, we will need to include 181 patients which is obtained in 12 clusters (six hospitals and six nursing home clusters). Taking into account a 20% dropout rate at 4 weeks due to the frailty of our study population, 228 patients are needed. Each participating center is therefore expected to include 19 patients.

#### Pilocarpine study

The sample size in this study was based upon our previous pilot study in older people with dry mouth [21]. By using the largest observed standard deviation from the pilot data (i.e. 3.8 points), we calculated a sample size of 57 patients per group, or 114 in total. Considering the low drop-out rates from previous studies with pilocarpine and the knowledge that in our study a less invasive administration method of pilocarpine is used, we expect limited loss-to-follow-up. However, to allow for some drop-out due to the frailty of the study population, the final sample size was set at 120 patients, with 60 patients per group.

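### The pilocarpine sample size of 57 per group is calculated for a difference in mean NRS, but the declared primary outcome is the percentage of responders, for which power is not stated

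*Protocol article*

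**What the plan says.** Under Primary outcomes, the Protocol article defines one primary outcome for both studies: "This is measured by the percentage responders at week 4, for which a clinically relevant response is defined as at least a 2-point reduction". The score in question is the NRS for dry mouth, from 0 to 10. Under Analysis of effect evaluation, the percentage of responders at 4 weeks is again named as primary, with the result expressed as an odds ratio and 95% confidence interval.

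The opening of Sample size gives the effect expected in both studies as "a minimum 2-point decrease on the 11-point numeric rating scale for dry mouth severity, as compared to CAU respectively placebo".

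The MEP paragraph then works with responders: a 25% difference in responders, "with a power of 0.8, an alpha of 0.05 and an intra cluster coefficient of 0.10". The pilocarpine paragraph does not. Its basis is "By using the largest observed standard deviation from the pilot data (i.e. 3.8 points), we calculated a sample size of 57 patients per group". The resulting total of 114 is raised to 120 (60 per group) as a margin for drop-out. The paragraph gives no responder rate, responder difference, alpha or power. The only significance level that covers the pilocarpine study is in the analysis section: a p "value < 0.05 will be considered to indicate statistical significance".

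**The concern.** The SD of a score sizes a comparison of mean scores. A comparison of two percentages needs the two percentages, and the pilocarpine paragraph gives neither. The 2 points also appear in two roles. Under Primary outcomes they are the drop that one patient must show to count as a responder. Under Sample size they become the difference expected between the groups. These are different quantities, and the second does not follow from the first.

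At stake is how a non-significant result would be read. Cutting a score at a threshold usually loses information, so a trial sized for the mean can have clearly less power for the responder comparison. A reader who takes the sample size section at face value would assume conventional power for the primary test, and could read a null responder result as evidence of no effect.

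**Working it through.** **Inputs from the article**
- Primary outcome: reduction of at least 2 NRS points at week 4 (Primary outcomes).
- Effect: 2 points versus placebo (Sample size, opening paragraph).
- SD: 3.8 points; 57 per group, 60 after the drop-out allowance (Sample size, Pilocarpine study).
- Alpha: 0.05 (Analysis of effect evaluation), taken as two-sided.
- Power: 0.8 is stated for the MEP study only; it is assumed here and tested by reproducing 57.

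**Step 1. Reproduce the plan's figure.** For two means, n per group = 2 × (1.96 + 0.842)² × (SD/difference)² = 2 × 7.85 × (3.8/2)² = 56.7, i.e. 57. The t-test version gives 57.6. Other common settings do not fit: one-sided 5% with 80% power gives 45, one-sided with 90% gives 62, two-sided with 90% gives 76. At 60 per group, power for the mean difference is 82%.

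**Step 2. Translate the same inputs into responder rates.** This needs assumptions that the article does not state: the reduction in NRS is normal, 3.8 is the SD of that change, pilocarpine shifts the mean by 2 points, and the placebo mean reduction is m. Then
- placebo responders = 1 − Φ((2 − m)/3.8)
- pilocarpine responders = 1 − Φ((2 − m − 2)/3.8) = Φ(m/3.8)

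With m = 0 this gives 29.9% and 50.0%, a difference of 20.1 points.

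**Step 3. Power for two proportions.** Power = Φ((d − 1.96 × SE0)/SE1), where d is the difference in responder rates, SE0 uses the pooled rate and SE1 the separate rates. For m = 0 and 60 per group:
- SE0 = √(0.3995 × 0.6005 × 2/60) = 0.0894
- SE1 = √((0.299 × 0.701 + 0.5 × 0.5)/60) = 0.0875
- power = Φ((0.201 − 0.175)/0.0875), about 61%

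**Step 4. Vary the placebo response, SD 3.8**

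| Placebo mean reduction | Responders, placebo v pilocarpine | Power, 57 per group | Power, 60 per group | n per group for 80% |
|---|---|---|---|---|
| −1 | 21.5% v 39.6% | 56% | 58% | 101 |
| 0 | 29.9% v 50.0% | 59% | 61% | 93 |
| 1 | 39.6% v 60.4% | 60% | 63% | 90 |
| 2 | 50.0% v 70.1% | 59% | 61% | 93 |

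Moving the cut to 1.5, to allow for whole-number scores, stays within these ranges.

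**Step 5. Vary the SD, 60 per group, 2-point shift, placebo mean reduction −1 to 2**

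| SD of change | Power for responders |
|---|---|
| 3.8 | 58–63% |
| 3.4 | 66–72% |
| 3.0 | 75–83% |
| 2.5 | 86–94% |

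**Step 6. Use a 25-point responder difference instead.** This is the MEP figure; the article does not state it for pilocarpine. For placebo rates of 10% to 50%, power is 77–90% at 57 per group and 79–92% at 60. With SD 3.8, a 2-point shift implies at most about 21 points.

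**The case against.** The mismatch itself is hard to dispute, but a reader might infer more from it than the article supports.

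**That the trial has 60% power.** The article does not show this. It gives no responder rates and does not say whether 3.8 is the SD of change or of a raw score. It calls 3.8 the largest SD seen in the pilot, so it was a cautious choice. The normal model is also rough here: with entry at NRS 5 or more on a scale that stops at 10, nobody can worsen by more than 5 points, yet a normal distribution with mean 0 and SD 3.8 puts about 9% of patients beyond that (Φ(−5/3.8) = 0.094). With a smaller SD or a 25-point difference, 120 patients are about enough. For instance, 25% v 50% responders needs 58 per group. All of this stands, so the power figure must be conditional. It does not remove the mismatch: the article names the SD, not a responder difference, as the basis of the 57.

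**That linear regression makes mean NRS the real primary outcome.** The analysis section does name linear regression for the pilocarpine study, but applies it to the percentage of responders and reports an odds ratio. It leaves the endpoint binary.

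**That the drop-out allowance is an error.** The step from 114 to 120 allows 5%, while the MEP paragraph writes "Taking into account a 20% dropout rate at 4 weeks due to the frailty of our study population". A reader might see a contradiction. The pilocarpine paragraph gives its own reasons, namely low drop-out in earlier pilocarpine studies and a less invasive route, and this study alone excludes patients whose mobility prevents correct use of the drops. Two studies may assume different losses.

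**That the primary outcome should be changed to mean NRS.** The case for this is greater power. Against it, recruitment began in June 2023, the article deliberately aligns outcomes across the two studies, and the responder criterion is the one it calls clinically relevant. The documents do not require the change.

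**Conclusion.** The concern holds as a mismatch between endpoint and calculation. The arithmetic is correct for a comparison of mean NRS, but that is not the declared primary outcome, and the 2-point responder threshold has been reused as a between-group mean difference. The implied 80% power is therefore unsupported for the primary test.

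How much power is lost depends on the unstated assumptions set out above. With SD 3.8 the shortfall hardly depends on the placebo response. With an SD near 3.0 or below, or a responder difference near 25 points, it largely disappears. The 80% target is itself inferred, from the reproduction of 57 and from the MEP paragraph.

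This should be fixed, but it is not fatal. It does not bias the estimate or invalidate the test; it bears on precision and on the reading of a null result. The planned 95% confidence interval and the stated emphasis on clinical relevance soften the consequence without correcting the text.

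**What to change.** Keep the percentage of responders at week 4 as the primary outcome. Before unblinding, restate the pilocarpine sample size paragraph so that it:

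1. says that 57 per group is a two-sided 5%, 80% power comparison of mean NRS (difference 2, SD 3.8), if the sponsor confirms those settings, and that it applies to the change in mean NRS, already listed under Secondary outcomes;
2. states the assumed placebo and pilocarpine responder rates and their source, for instance the pilot data;
3. gives the resulting power at 60 per group over a range of SDs or responder differences, as in Steps 5 and 6;
4. separates the within-patient responder threshold from the between-group difference in the opening sentence of Sample size.

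Power under higher loss than 5% may be added as a sensitivity figure.

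The cost is protocol or analysis plan wording and one short calculation, with no extra patients, visits or data. The stated power for the primary outcome may turn out less favourable than the article now implies, and a null result would then have to be interpreted in that light.
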